### Recruitment {15}

Participants are recruited through:The participating health insurance (BARMER)Physicians, psychologists, and physical therapists within regional networksThe study centres

The recruitment of insured individuals and patients, as well as their referral to the project, is carried out by the consortium partners’ project management, the PAIN2.0 centres themselves as well as by cooperating clinicians (general practitioners, specialists, company physicians and other health professionals). Recruitment measures are implemented in a systematic rotation and are repeated in conjunction with new information. The recruitment process spans a period of 5 or 6 months, with the first patient being enrolled in January 2023.

### Recruitment of referring clinicians

An important factor of early patient care is the timely identification of risk factors by healthcare providers (including general practitioners, specialists, company physicians, orthopaedists, neurologists, physiotherapists, and other health professionals). With the support of the project team (e.g. collection of contact data of potential referrers), PAIN2.0 centres contact patients directly (in person, by telephone, by post), organise information events or collaborate with the regionally established general practitioner training activities and quality circles of various specialist groups (including pain conferences). This network effort is aimed at ensuring the sustainability of the new care service and thus is an important component of the project protocol.

Further, the consortium leader Deutsche Schmerzgesellschaft e.V. will contact national networks of potential referring professions and provide information about the study and intervention.

### Recruitment of patients

Patient recruitment for the A-IMPT primarily relies on press releases and the websites of the participating centres. In addition, BARMER sends informative mail to insured individuals, based on healthcare data suggesting the onset of developing chronic pain. These individuals will have the option to contact BARMER’s specifically trained telephone counselling service (‘teledoctor’). The staff members of teledoctor perform a preliminary check of initial inclusion and exclusion criteria and refer the insured individual directly to the centre or provide the centre’s contact details. Other methods of patient recruitment include direct contact with PAIN2.0 centres through flyers, posters, newsletters, local advertising measures or activities on social media [35]. Patients can also reach out to the centre directly.

### Recruitment via public relations work

The wider public is informed about PAIN2.0 through the homepage [36], national press releases, publications in specialised media (which not only highlight the unique aspects of the patient group but also describe the innovative A-IMPT care service), outreach to associations, medical associations and businesses as well as advertising on social media platforms. These initiatives are coordinated by the consortium partners’ project management. Interested referring clinicians and patients can contact the PAIN2.0 centres directly.

In preparation for recruitment, numerous recruitment options were presented to the centres in video conferences, and sufficient materials for implementation were handed out (including cover letters, webinars and regional press releases). During the recruitment phase, support and exchange were offered to the centres in video conferences or in the context of individual centre support. To ensure the consistency of project communications, the project team developed text modules that were tailored to different target groups, including patients, the professional public, and the general public. These modules were applied in a standardised manner.

### Assignment of interventions: allocation

#### Sequence generation {16a}

Lists of randomised blocks of varying lengths were generated by the evaluating institute for each participating centre and implemented in the PAIN2.0 database.

### Concealment mechanism {16b}

Lists of randomised blocks used in the external randomisation were not known to the recruiting centres at the time of patient enrolment.

### Implementation {16c}

Patients are enrolled by physicians who verify the primary inclusion and exclusion criteria.

Those patients who fulfil both the primary and secondary inclusion criteria and have no reasons for exclusion are consecutively included in the study.

Patients providing informed consent were randomly assigned to the intervention or control group by the medical documentarians during study enrolment.

## Assignment of interventions: blinding

### Who will be blinded {17a}

N/a. Blinding is not possible.

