#### PAIN2.0

PAIN2.0 is a consortium project of the Innovation Fund (01NVF20023) with a duration of 42 months.

The consortium leader is the German Pain Society (Deutsche Schmerzgesellschaft e.V.). The consortium partners involved in the project management (PM) are a public health insurance provider (BARMER), an external evaluation institute (Institute for Community Medicine, University Medicine Greifswald), as well as four institutions with profound experience in delivering interdisciplinary multimodal pain therapy (IMPT) (German Red Cross Pain Centre Mainz, University Hospital Carl Gustav Carus Dresden, University Hospital Schleswig-Holstein/Lübeck, University Medical Centre Göttingen).

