### Strategies to improve adherence to interventions {11c}

Before the start of recruitment, the centres receive training in the interventions, study documentation and data management, utilisation of assessment instruments, transmission of study documentation to the evaluating institutions, as well as the procedures and obligations regarding data validation. Training is mandatory; furthermore, written and video-based training materials are accessible through an access-restricted website.

A comprehensive monitoring concept has been developed and will be executed by the project administration (Deutsche Schmerzgesellschaft e.V.) in collaboration with consortium partners, including the German Red Cross Pain Centre Mainz, University Hospital Carl Gustav Carus Dresden, University Hospital Schleswig-Holstein/Lübeck, University Medical Centre Göttingen, and the evaluating institution (University Medicine Greifswald). The monitoring aims to oversee the implementation and adherence to the study protocol, provide direct feedback to the centres, and document any relevant deviations. It commences immediately after the recruitment and inclusion of the first patients.

For participants of the control group, an intermediate medical visit (interim contact) is scheduled after 3 months to prevent dropout. In addition to reassessing the status of the inclusion and exclusion criteria, a brief status report on the patient’s condition is given, and the patients should be motivated to attend the later intervention.

The principle of data management and monitoring has been described in a comprehensive data management plan.

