### Procedure for unblinding if needed {17b}

N/a. There is no blinding.

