### Methods in analysis to handle protocol non-adherence and any statistical methods to handle missing data {20c}

In longitudinal analyses involving more than one follow-up time point, the family of (generalised) mixed models uses all available data, even if data at some time points are missing. If necessary (e.g. in case of high drop-out-rates > 30%), appropriate methods of (multiple) imputation of missing values will be employed. The population for primary analysis includes all patients for whom PI and DS data are available at baseline and at 6-months-follow-up.

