### Trial status

Protocol version number: study protocol version 1.3 dating from 04/09/2022.

Start of recruitment: 01/01/2023.

End of Recruitment: 28/02/2024.

A revision of the study protocol became necessary as bottlenecks in the planned recruitment numbers arose during the recruitment process. The modification relates in particular to the reduction of the primary endpoints to two. Pain intensity and pain-related functional impairment (Von Korff Index) are defined as primary endpoints. Patient satisfaction is now only analysed as a secondary endpoint. The revision enables an appropriate and meaningful evaluation study despite a noticeable reduction in the number of cases.

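### The protocol rules out blinding for every role, although the analyst of the primary comparison could be masked, and it describes no separation between list-holding, monitoring and analysis at the evaluating institute

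*Protocol article*

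**What the plan says.** - **Blinding.** Who will be blinded {17a} reads "N/a. Blinding is not possible", and Procedure for unblinding if needed {17b} reads "N/a. There is no blinding". No role is distinguished and no reason is given.
- **Allocation lists.** On sequence generation, item {16a} of the article states: "Lists of randomised blocks of varying lengths were generated by the evaluating institute for each participating centre and implemented in the PAIN2.0 database". The next item, {16b}, says the lists were unknown to the recruiting centres at enrolment. It does not mention the analyst.
- **Who the institute is.** The section PAIN2.0 names, among the partners in project management, "an external evaluation institute (Institute for Community Medicine, University Medicine Greifswald").
- **Monitoring.** Strategies to improve adherence to interventions {11c} lists among those who monitor "and the evaluating institution (University Medicine Greifswald). The monitoring aims to oversee the implementation and adherence to the study protocol". Section {18a} repeats this, and the project management group described under {21a} includes the same university.
- **Analysis.** The auditing section {23} has the data delivered to the evaluation institute and the project team for final analyses. The dissemination section {31a} calls the institute independent.
- **Open choices.** Statistical methods {20a} allows further predictors if relevant differences between the arms appear despite randomisation. Section {20c} says that, if necessary, "appropriate methods of (multiple) imputation of missing values will be employed". Drop-out above 30% is given there only as an example of when.

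**The concern.** Item {17a} asks about each role, and the answer excludes all of them. This is a positive statement, not a silence that a separate analysis plan could fill: a plan with a masked analyst would contradict {17a} and {17b}. For the analyst, the statement that blinding is impossible is wrong.

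What is at stake is modest but avoidable. If the covariate set or the handling of missing data is settled by someone who can see which arm is which, the choice can lean towards the intervention, even without intent. The primary outcomes are patient-reported in an open trial and so already exposed to expectation effects. A second route to bias need not be left open when closing it costs little.

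**Working it through.** The plan gives no figure on this point, so there is none to reproduce. The check has two parts.

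**1. Can the primary analyst be masked?** Statistical methods {20a} sets out the primary model: the 6-month value of pain intensity (PI) or disability score (DS) on the baseline value and group membership, with a random intercept. The file therefore needs:
- baseline and 6-month PI and DS;
- the identifier for the random intercept (presumably centre; the section does not name the level);
- a group label.

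None of these reveals the arm if the label is coded A/B. Some other records would: the fifth-week process questionnaire, session attendance, the control group's 3-month interim contact, and the items on satisfaction with the intervention. None of them is needed for the primary model, so masking is feasible for this analysis. It may not be for the full data set.

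**2. What could a choice leaning towards the intervention do?** The assumptions are:
- two defensible versions of the primary analysis;
- test statistics Z1 and Z2, standard normal under no effect, positive favouring the intervention;
- correlation r = 0.9, which is not in the documents;
- the version with the larger Z is reported.

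At two-sided 0.05 the critical value is z = 1.960, and P(both > z) = P(both < −z) = 0.0148.

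- False claim for the intervention: P(max > z) = 2 × 0.025 − 0.0148 = 0.0352, against 0.025 with one fixed analysis.
- False claim against it: P(max < −z) = 0.0148, against 0.025.
- Two-sided total: 0.0352 + 0.0148 = 0.0500, unchanged.

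The same calculation over a range of r and at the Bonferroni level for two endpoints (0.05/2 = 0.025):

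| Two-sided level | r | P(both > z) | False claims for the intervention | With one fixed analysis |
|---|---|---|---|---|
| 0.05 | 0.80 | 0.0110 | 0.039 | 0.025 |
| 0.05 | 0.90 | 0.0148 | 0.035 | 0.025 |
| 0.05 | 0.95 | 0.0177 | 0.032 | 0.025 |
| 0.025 | 0.90 | 0.0069 | 0.018 | 0.0125 |

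A different behaviour is to report whichever version has the smaller p-value, in either direction. At level 0.05 and r = 0.9 this gives about 2 × 0.0352 = 0.070. It needs no knowledge of which arm is A and which is B, so coding the arms does not prevent it. Only fixing the choices before any group comparison does.

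**The case against.** The strongest case on the other side has five parts.

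- **The main bias is untouched.** Patients know their arm and report their own outcomes. Masking the analyst does nothing about that. This stands, and it limits the benefit.
- **The core model is already fixed.** {20a} states it, and a separate analysis plan may settle covariates and imputation. The example trigger for imputation, overall drop-out above 30%, can be judged without knowing arms. This stands in part: the trigger is only an example, and the covariate option depends on looking at differences between the arms.
- **Overlap is shown only at institute level.** A reader might infer that every open choice is made by people who know the arm codes. The article does not say who makes these choices or when, nor that one person both holds the lists and analyses the data. What can be said is that no separation is described.
- **Some open choices are peripheral.** The distributional model for sick-leave and cost data concerns secondary outcomes, and the grouping of centres is declared exploratory. Neither supports a point about the primary result.
- **The endpoint revision.** A reader might infer that reducing the primary endpoints from three to two in an open trial was guided by outcomes. The documents do not support this. Trial status gives a recruitment reason: "A revision of the study protocol became necessary as bottlenecks in the planned recruitment numbers arose during the recruitment process". The sample size section places the shortfall in the initial phase of the project, and no interim analysis is planned. Masking the final analyst would not have affected that decision.

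**Conclusion.** The point holds in a limited form. The total exclusion of blinding in {17a} and {17b} is wrong for the analyst of the primary comparison. The article places list generation, a share of monitoring and the evaluation at one institute without describing a separation, while covariates and imputation remain open.

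The size is small. Under the assumed pair of analyses, false claims for the intervention rise from 0.025 to about 0.035 (0.032 to 0.039 for correlations of 0.95 to 0.80) at two-sided 0.05. A reader might infer that the two-sided error itself rises above 0.05. Under direction-favouring choice it does not, and the rise to about 0.070 from picking the smaller p-value is not something arm coding would cure.

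The calculation rests on the assumed number of analyses, their correlation and the selection rule, none of which the documents give. This is a desirable improvement, not a defect that threatens the trial.

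**What to change.** Restate {17a}: patients and therapists are not blinded, outcomes are self-reported, and the primary analysis is done by a statistician masked to arm. Bring {17b} into line by saying when and by whom the codes are released. Then:

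1. Someone at the evaluating institute who takes no part in the analysis holds the lists and supplies a file of baseline and 6-month PI and DS with coded groups. Arm-revealing records (the fifth-week form, session records and interim-contact records) are left out.
2. The covariate set, the imputation decision, the model and the code are fixed and dated before any between-group comparison is run, and before the codes are released. The first condition controls selection by p-value; masking controls selection by direction.

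The cost is a paragraph of text, a short data-preparation step, and keeping list-holding apart from analysis within the institute. The change is still possible for any analysis not yet run.

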### Procedure for unblinding if needed {17b}

N/a. There is no blinding.

### Data collection and management

#### Plans for assessment and collection of outcomes {18a}

Prior to the start of recruitment, the participating centres will receive training on the interventions, the utilisation of assessment instruments, handling the study documentation, forwarding the study documentation to the evaluating institutions, and the process and obligations for data validation.

At the time of enrolment (i.e. before *t*_0_), patients will be asked to complete the standard questionnaire of the German Pain Society (DSF) [37]. In addition, medical data is assessed. Further data collection is done through questionnaire surveys at baseline and at 3-, 6-, 9- and 12-month follow-ups. In addition, a process evaluation questionnaire is to be completed in the fifth week of the intervention (Fig. 4).

Data is archived in a PAIN2.0 database, which contains all documentation.

Monitoring is conducted by the central project coordinator (Deutsche Schmerzgesellschaft e.V.), the consortium partners German Red Cross Pain Centre Mainz, University Hospital Carl Gustav Carus Dresden, University Hospital Schleswig-Holstein/Lübeck, University Medical Center Göttingen, and the evaluating institution (University Medicine Greifswald).

Questionnaires are available at the German Pain Society (Deutsche Schmerzgesellschaft e.V.).

*Plans to promote participant retention and complete follow-up {18b}*

To promote participant retention, several procedures have been introduced. Participants in the intervention group receive one individual contact with each professional group during the 10-week therapy. These individual contacts last 30 min each and can be split into two appointments of 15 min each if necessary. Participants in the control group receive an additional intermediate medical visit after 3 months to prevent dropout. The questionnaire response is monitored through the database. If a questionnaire is not returned on time, two follow-up actions are taken. Patients who do not regularly attend the interventions will be contacted by the study centre. Reasons for discontinuation are documented.

A list of outcome data will be compiled for participants who discontinue or deviate from the intervention protocols. This will include detailed information on participants who drop out of the intervention or deviate from the study protocol.

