### Outcomes {12}

#### Primary outcomes

The primary outcomes are (1) characteristic pain intensity (PI) and (2) disability score (DS) for pain-related impairment. PI and DS are collected at baseline (*t*_0_) and at 3-, 6-, 9- and 12-month follow-up (*t*_1_ to *t*_4_). Changes in the primary outcomes between baseline (*t*_0_) and 6-month follow-up (*t*_2_) are evaluated as primary endpoints. Data are collected through a patient questionnaire, which includes the following:

(1) Characteristic pain intensity and (2) disability score are components of the Von Korff Chronic Pain Grade Scale (CPGS) [16]. The CPGS is a multidimensional measure with 7 items covering the two mentioned dimensions of overall chronic pain severity. The PI score is calculated as the average of three 0–10 ratings for ‘pain right now’, ‘average pain’ and ‘worst pain’, which is then multiplied by 10 to obtain a 0–100 score. The DS score is derived from the average of three 0–10 ratings for ‘daily activities’, ‘social activities’, and ‘work activities’, also multiplied by 10 to produce a 0–100 score. The last item covers the disability days.

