### Statistical methods

#### Statistical methods for primary and secondary outcomes {20a}

The primary analysis model for the two primary outcomes (pain intensity and disability score at 6 months adjusted for baseline values) is a linear mixed regression model with a random intercept.

The values of the primary outcomes at time *t*_3_ (6-month follow-up) serve as the dependent variables. To describe the effect of the intervention, the baseline value at time t_0_ and group membership are used as predictor variables [38, 39]. As two primary endpoints are analysed simultaneously, adjustment for multiple testing using Bonferron’s method will be applied.

When using these models, it is possible to include further predictor variables in the analysis. This can be of interest if, despite randomisation, relevant differences occur between the study arms and must be statistically controlled, or if the effects of covariates (e.g. of age or other patient characteristics) are to be analysed. Through appropriate model specification, all hypotheses of interest can be tested with these analysis methods.

The analysis of the primary endpoints will be conducted according to the intention to treat (ITT) principle.

The primary and secondary outcomes to be investigated are predominantly continuous data for which linear regression models can be used. However, the family of (generalised) mixed models also allows analogous evaluations for other types (ordinal or categorical) of dependent variables.

In the context of the analysis of days of incapacity to work or cost data, it may furthermore be necessary to use special analysis methods for data with an asymmetric distribution or with heavily populated zero cells (‘zero-inflated’).

Statistical significance tests are performed with an α-level of 0.05 (two-sided). In the confirmatory analysis of the primary outcome measures, a Bonferroni adjustment for multiple testing (3 outcome measures, 2 follow-up times) is applied. No such adjustment is used in the exploratory analyses of the secondary outcomes.

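### The protocol implies, without stating it, that self-reported t0 pain and disability scores may be collected after allocation in an unblinded trial, yet t0 is both the primary covariate and an entry condition for the primary analysis

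*Protocol article*

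**What the plan says.** Four parts of the protocol article bear on the order of events.

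- **Randomisation.** Implementation {16c}: "Patients providing informed consent were randomly assigned to the intervention or control group by the medical documentarians during study enrolment".
- **Enrolment and baseline.** Plans for assessment and collection of outcomes {18a}: "At the time of enrolment (i.e. before *t*_0_), patients will be asked to complete the standard questionnaire" of the German Pain Society. It continues: "Further data collection is done through questionnaire surveys at baseline and at 3-, 6-, 9- and 12-month follow-ups".
- **What t0 is.** Primary outcomes: "PI and DS are collected at baseline (*t*_0_) and at 3-, 6-, 9- and 12-month follow-up". Both scores are self-reports: "Data are collected through a patient questionnaire, which includes the following".
- **Blinding.** Section {17a}: "N/a. Blinding is not possible".

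Two parts say how t0 is used. In the primary model of {20a}, "the baseline value at time t_0_ and group membership are used as predictor variables". Section {20c} sets the analysis set: "The population for primary analysis includes all patients for whom PI and DS data are available at baseline and at 6-months-follow-up". Section {20a} also says that the primary endpoints are analysed by intention to treat.

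**The concern.** A baseline value is a safe adjustment covariate because randomisation cannot have influenced it. That protection is lost if the patient already knows whether therapy starts now or after a six-month wait when rating pain and disability. Relief or disappointment could move the ratings differently in the two arms, and the model would then adjust for something that allocation had partly caused.

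The analysis set raises a related problem. If t0 precedes allocation, a missing t0 cannot depend on the arm, so dropping such patients costs numbers but does not bias the comparison. If t0 follows allocation, a patient who loses interest on learning of the wait and never returns the form leaves the primary analysis because of the arm assigned. Both routes reach both primary endpoints.

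**Working it through.** **Step 1: order of events.** The plan gives no figure to reproduce, so the sections are set side by side.

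1. {16c}: allocation takes place within enrolment, after consent.
2. {18a}: enrolment lies before t0. The enrolment questionnaire and medical data belong to it.
3. {18a}: the baseline survey is listed as further data collection, alongside the follow-up surveys.
4. On the natural reading of 1 to 3, allocation comes before t0.
5. Nothing in the readable text puts completion of t0 before allocation is generated or disclosed. Concealment mechanism {16b} keeps the lists from the centres at enrolment. That protects who is enrolled, not a self-report made later.

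**Step 2: effect on the primary model.** Let d be the between-arm difference in mean t0 that knowledge of allocation causes (intervention minus control), and b the within-arm slope of the 6-month score on t0. The baseline-adjusted group effect is then biased by −b × d. The document gives neither b nor d, so the values below are assumptions.

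| Assumed b | Assumed size of d (points) | Size of bias (points) |
|---|---|---|
| 0.4 | 3 | 0.4 × 3 = 1.2 |
| 0.6 | 5 | 0.6 × 5 = 3.0 |

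For scale, Sample size {14} targets a difference of 0.3 in standardised change. With an assumed SD of change of 20 points this is 0.3 × 20 = 6 points, so the range is 1.2/6 = 20% to 3.0/6 = 50% of the target.

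**Step 3: effect on the error rate.** Trials were simulated with no treatment effect, 250 patients per arm (half of the 500 in {14}), a two-sided level of 0.05/2 = 0.025 for two primary endpoints, and 3,000 runs per setting. At an assumed baseline-to-6-month correlation of 0.5, where the SD of change equals the SD of the score:

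| Assumed shift d (SD) | Size of bias (SD) | Share of 0.3 target | Rejection rate at nominal 0.025 |
|---|---|---|---|
| 0.1 | 0.05 | 17% | 0.057 |
| 0.2 | 0.10 | 33% | 0.185 |
| 0.3 | 0.15 | 50% | 0.381 |

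Over correlations of 0.4 to 0.6 and shifts of 0.1 to 0.3 SD, the rejection rate ran from 0.045 to 0.589. With d = 0 this source adds no bias and the level holds.

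**Step 4: cost of leaving t0 out.** An analysis of the 6-month score without t0 is untouched by a shift in t0. Relative to adjustment for a sound baseline, its standard error is larger by 1/√(1 − r²): 1.09 at r = 0.4 and 1.25 at r = 0.6 (r assumed).

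**The case against.** The strongest objection is that no section says t0 follows randomisation. Enrolment is described as a process with several steps, and the clause in {18a} dates the enrolment questionnaire, not the allocation. An enrolment questionnaire first, then t0, then allocation would fit {16c}, although {18a} reads less naturally that way. Participant timeline {13} refers to Figure 4 for the full schedule, and that figure and Figures 1 and 2 are not in the copy reviewed. The article also condenses a fuller protocol. All of this stands and limits the point to an inferred order. If the figures do put t0 first, {16c} and {18a} still need wording that agrees with them.

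The bias also requires that patients learn their arm before completing t0, and the article is silent on when they do. That stands too.

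A further objection is that the complete-data rule in {20c} sits badly with intention to treat whatever the timing. This is true, and the 6-month half of the rule is a separate matter. The timing decides whether the baseline half can bias the comparison or only reduces numbers.

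Finally, therapy expectation, measured only at t0, is not in the planned primary model. This is right: it matters only if it is added under the option in {20a} to include further predictors.

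A reader might infer that baseline was definitely taken from patients who knew their arm, or that the effect estimate is off by 20% to 50% of the target. The documents support neither: the order and the disclosure are not stated, and those percentages rest wholly on assumed inputs.

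**Conclusion.** The concern holds as a risk that the text creates and does not rule out. On their natural reading, {16c} and {18a} allow the self-reported t0 scores to be collected after allocation in an unblinded trial. If they were, the primary covariate can be affected by allocation, and the t0 requirement in {20c} becomes a post-randomisation exclusion that conflicts with the intention-to-treat statement in {20a}.

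Neither the direction nor the size of any bias can be read from the document. The illustrative 1.2 to 3.0 points depend on the assumed slope and shift, and their comparison with a 6-point target also depends on the assumed SD of change. The point should be fixed, but it falls short of a must-fix because the order is inferred and may prove to be sound.

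**What to change.** Trial status gives the end of recruitment as 28/02/2024, so conduct cannot be changed. The remedy lies in wording, a date check and the analysis.

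1. Reconcile {16c} and {18a}: state whether the t0 questionnaire was completed before or after allocation, and when patients were told their arm.
2. Compare t0 completion dates with randomisation dates. Report by arm how many t0 forms came after allocation and how many are missing.
3. Remove the t0 condition from the primary population in {20c}. Keep randomised patients with missing t0, for example by imputing the baseline.
4. If some t0 forms came after allocation, add a pre-specified sensitivity analysis for both primary endpoints. It should either leave t0 out of the model or be restricted to a PI/DS value dated before randomisation, where one exists. The article does not say whether the enrolment questionnaire supplies such a value.
5. Do not use therapy expectation as an adjustment covariate where it was recorded after allocation.

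The cost is a few sentences, a check of dates (assuming the database records them), a little extra analysis, and some loss of precision in the sensitivity analysis, as worked out above. No new data collection is needed. If every t0 form preceded allocation, step 1 and the reported check settle the question of bias from t0.
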